### Structural interventions

These are embedded in clinical and socio-behavioural communication components. The clinical knowledge and expertise of HCWs, as well as their knowledge of HIV and TB stigma should be strengthened by having a clinician assist them with their cases. A positive outcome we anticipate from this is that health systems will be strengthened by an improved environment in which HCWs can seek care in the workplace.

Knowledge of key infection control practices, and distribution of information on HIV and TB stigma-related rights and responsibilities in the healthcare workplace, including where to go for help and how to report transgressions of HCW rights—are all examples of structural issues embedded in training sessions.

### Social and Behavioural Change Communication (SBCC) interventions

These are the priority interventions and comprise two components: training HCW change agents, and a social marketing campaign.

#### The main SBCC intervention is training HCWs to reduce HIV and TB stigma in their workplace

This is underpinned by social theory of the Diffusion of Innovations [25] proposed by Everett Rogers. The theory sets out to explain how, why, and at what rate, new ideas and technologies spread. He proposes that social change is accelerated via change agents: individuals who are seen as role models. People look up to them and regard their choices and actions as admirable and worthwhile emulating. As a consequence of this esteem, they are ideally positioned to promote change and the diffusion of new ideas and practices in social and organisational contexts [40]. This social theory of Diffusion of Innovations has been applied to stigma among HCWs in other settings [22–24].

The research design regards *all* HCWs as contributing to, and thus co-constructing, their workplace community and its social norms. Accordingly, change agents need to be identified across the entire workplace, and from all three occupational categories: clinical staff (e.g. physicians, nurses, allied health workers); managerial and administrative staff; and support-services staff (e.g. cleaners, laundry workers, housekeeping, porters) (SPIRIT point 10; see also ‘Section 3.4’). Adopting multiple methods for selecting change agents helps to identify ‘informal’ as well as ‘formal’ leaders and yields candidates across a wide social spectrum; thus, a two-pronged sampling approach—*positional* and *snowball*—will be followed to identify and recruit them [41].

Positional sampling involves selecting individuals based on the formal leadership positions that they hold in their hospitals. An advantage is they are well-positioned to promote change. A drawback is that only those in formal leadership positions are accessed. To remedy this Valente and Pumpuang [41] suggest combining positional with snowball sampling. In snowball sampling the pool of change agents serves as a sociometric sample that provides information for locating other potential change agents.

The first set of individuals—the ‘index cases’— are identified via positional sampling. We ask hospital CEOs to provide a list of their most influential staff across all three staff categories, e.g. top and middle managers (including the CEOs themselves), members of the hospital committees, occupational health nurses, health and safety representatives, social workers, and so forth. We then hold an information meeting for these positional leaders and invite them to act as change agents. In the first iteration of snowball sampling, they are also asked to nominate other staff who they think are role models in their facility and who they think are likely to be effective in helping to reduce stigma; nomination can be vertical or horizontal in terms of levels of hierarchy and occupational categories. These new nominees are then approached by fieldworkers and the intervention team leader, invited to be change agents, and also asked to nominate others. This snowballing process is repeated until the required number of change agents is recruited. *As usual, informed consent must be obtained from all who agree to participate (SPIRIT point 32)* (Additional file 3). In terms of process, the names of consenting nominees and other relevant information are entered into an Excel spread sheet by the research and implementation teams (SPIRIT point 16a). All consenting nominees appearing in the Excel sheet are then invited by team members to participate in stigma-reduction training at selected dates (SPIRIT point 16c).

It is estimated that a sample of 40–50% from each staff category—clinical, management and administration, and support services—is needed to effect measureable change in their hospitals (SPIRIT point 14). Half of the required proportion of participants were contacted for the first round of training in all four intervention hospitals; the second half will be contacted in September 2017 for the second round of training. We split the training into two rounds because we did not want any one hospital to lag behind too much in terms of obtaining the first full ‘dose’ of the intervention; this is more equitable in terms of time, which is important given that we do not have as much intervention time as we initially anticipated (see the ‘Discussion’ section). The estimated number of change agents for training in each intervention hospital appears in the addenda (Additional file 4). For the first round of training the required sample size was reached after the second round of peer nominations (snowball sampling). It is anticipated that the same will occur for the second round of training (SPIRIT point 15; see also ‘Section 2.3.2’).

It is important to note that, in order to minimise disruption of service delivery, training times are arranged in consultation with hospital representatives/management.

Training sessions are standardised as much as possible. Facilitators practice together and deliver the training strictly adhering to a facilitator’s training manual [42], reviewed by peers, and translated (as well as back-translated) into the three local languages. To minimise impact on the workplace, a training session lasts only 4 h. On completion of the training participants evaluate the training and receive a certificate of attendance. Training follows best practice in terms of content and processes that are highly interactive and lively, designed for adult-based learning and for engaging participants at the levels of knowledge, emotion, and action.

At first we planned to train participants in separate groups depending on their job categories. But, as our pilot training sessions showed, this is not possible because one cannot take too many clinical professionals, for instance, away from their posts at one time. We were also advised that splitting sessions into people from one job category could be stigmatising in itself, and constrain the abilities of people at different levels in the hierarchy to communicate and learn from one another about an issue which transcends job categories. We thus divided trainees into groups in terms of one main criterion: their preferred language of instruction (SPIRIT point 16a). Trainees who did not have a particular language preference were allocated to training sessions according to their expressed preference for certain dates and times.

What is unique to the training is that it builds on ordinary human compassion, expressed in caring *communication*. So, there is no monetary or infrastructure costs. Change agents are encouraged to start conversations about HIV and TB stigma in the workplace with co-workers, and/or respond to stigmatising situations they encounter in the workplace, in ways that feel *natural* to them. They do receive some social marketing materials (e.g. branded wristbands and pens) to support their stigma-reduction communications, and there is also the wider, visible social marketing campaign (especially the posters) that they can point to in order to spark conversations or highlight what they are saying.

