Although the *processes* described in this section are similar for recruiting survey respondents and intervention participants, the latter are not sampled in the same way. Selection for interventions is described in the next section.

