## Data collection and management (SPIRIT point 18a)

Fieldworkers experienced in health research are used for all data collection stages and given additional training to sensitise them to the requisite quality and standardisation of research processes. In the case of qualitative work, fieldworkers work side-by-side with CHSR&D research team members.

Small tokens of appreciation in the form of a shopping voucher (for R50; approximately US$4) and small gifts (chocolates, pens, and wristbands branded with the imagery and slogan of the social marketing campaign) are supplied to fieldworkers and researchers to give to participants who complete the surveys, participate in focus groups/ one-on-one interviews, or attend the change-agent training.

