### Baseline data collection

Once the fieldworkers track down the randomly selected individuals and obtain informed consent from those willing to participate (described earlier in the section ‘Participants’ sub-section ‘Recruitment’) (*SPIRIT point 32*), (Additional file 3), they hand each participant an envelope with the stigma questionnaire—to be self-administered. Fieldworkers either wait for a respondent to fill in the questionnaire, or arrange a time and place to collect the completed questionnaire from the respondent if it is not convenient for the respondent to fill it in immediately. Respondents with low levels of reading literacy are gathered into small groups, the fieldworkers work through the questions verbally *with the whole group*, and address any queries with the whole group; however, respondents have to fill in the questionnaires themselves.

When the respondent hands in their completed questionnaire, the fieldworker quickly scans through each one to check for completion (not to see the person’s actual answers). Where substantial sections of the questionnaire are not completed, the fieldworker marks the places and hands it back to the respondent to complete properly. This helps to ensure that the dataset is not overly compromised by being incomplete.

As described in the ‘Ethics’ section, respondents’ names are replaced with a unique number that is pasted onto their consent forms, their completed survey questionnaires, and the participant list kept by the fieldworkers. Each day, the lists, consent forms, and completed questionnaires are handed to fieldwork team leaders, who are responsible for collating information at the end of each day (i.e. how many respondents are reached, number of questionnaires completed/outstanding, and highlighting which respondents still need to be reached). The fieldwork teams maintain telephone contact with the CHSR&D on a daily basis and once a week they meet face-to-face with one of the project principal investigators (PIs). The purpose of this meeting is to report back on progress, any difficulties experienced, and hand in completed questionnaires.

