### Post-intervention data collection

The same processes and protocols are followed for the post-intervention survey. Respondents from the baseline survey are tracked down via their unique identifiers and asked to complete the post-intervention questionnaire. As noted before, there was a 50% oversampling of respondents to allow for loss-to-follow up between baseline and post-intervention surveys (SPIRIT point 18b).

To ensure comparability, the post-intervention survey will resemble the pre-intervention survey, thus including the HIV/AIDS and TB stigma scales as well as the range of other key outcome measures related to stigma at the individual, community, and structural levels—as described above. The post-intervention survey will also have a new section to measure the reach and appeal of the stigma interventions.

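### The article lets fieldworkers both recruit change agents and collect the self-reported stigma outcome, so reporting bias may be larger in the intervention arm

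*Protocol article*

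**What the plan says.** Recruitment to the intervention is described under the heading on training HCWs to reduce stigma. Hospital leaders are invited at an information meeting and nominate colleagues, and then "These new nominees are then approached by fieldworkers and the intervention team leader, invited to be change agents". This takes place only in the intervention arm: "Half of the required proportion of participants were contacted for the first round of training in all four intervention hospitals". The target is given as "It is estimated that a sample of 40–50% from each staff category".

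Measurement is described under Data collection and management, where "Fieldworkers experienced in health research are used for all data collection stages". Under Baseline data collection, "they hand each participant an envelope with the stigma questionnaire—to be self-administered". The fieldworker may wait while the form is filled in. On return the fieldworker scans it for completeness, with the stated intention of not looking at the answers, and hands it back if large parts are blank. For respondents with low reading literacy, small groups are formed and "the fieldworkers work through the questions verbally", although each person marks their own form. Post-intervention data collection carries these procedures over and adds that "The post-intervention survey will also have a new section to measure the reach and appeal of the stigma interventions".

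The closing sentence of Recruitment says that the processes "are similar for recruiting survey respondents and intervention participants, the latter are not sampled in the same way". The contrast drawn there is about sampling, not about who does the work.

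**The concern.** The primary comparison rests on attitudes that respondents report about themselves, and the campaign teaches which answer is the kind one. If the person who asked a staff member to promote that message later hands over, checks or reads out the stigma questionnaire, that staff member has an added reason to answer in line with the message. Control hospitals have no change-agent recruitment, so this source of bias does not cancel between arms. Reported stigma could fall in the intervention arm by more than stigma itself, and the mixed model planned for the follow-up data cannot tell the two apart.

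**Working it through.** **1. The two roles side by side**

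- Inviting nominees to be change agents: fieldworkers with the intervention team leader, in the four intervention hospitals only.
- Collecting the outcome: fieldworkers, at every data collection stage, in all eight hospitals.
- Separation of the two: none described. The article mentions research and implementation teams in several places, but it gives the invitation task to fieldworkers and has both teams enter nominees' details.
- Blinding of collectors to arm: none described. With campaign posters displayed throughout the wards, it would be hard to achieve on site.
- Protection at completion: self-completion, an envelope (not described as sealed) and a number in place of a name. The same number is also pasted on the consent form and on the fieldworker's participant list.

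The plan therefore permits overlap. It does not state that overlap occurs.

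**2. What could cue each arm**

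- Previous contact with a recruiter: possible only in intervention hospitals.
- Reach-and-appeal section: part of the follow-up survey, with no restriction by arm and no stated position on the form.
- Gifts carrying the campaign slogan and image: given to people who complete the surveys, with no restriction by arm.

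The last two can reach controls as well. A shift common to both arms cancels, so only the net difference in shift between arms matters.

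**3. The plan's own figure**

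Inputs from Sampling: means 0.85 and 0.65 (difference 0.20), SDs 0.71 and 0.39, two-sided alpha 0.05, power 90%.

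n per arm = (1.960 + 1.282)² × (0.71² + 0.39²) / 0.20² = 172.4, rounded up to 173. This matches the article. Then 173 × 1.7 = 294, against 292 stated, which is agreement to within rounding of the design effect.

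**4. What a net reporting shift would do (assumed values)**

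The documents give no size for a demand effect. Let b be the net shift in reported score between arms when the true effect is zero. With 173 effective respondents per arm:

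SE = √[(0.71² + 0.39²) / 173] = √(0.6562 / 173) = 0.0616

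False-positive rate = Φ(−1.96 + b/SE) + Φ(−1.96 − b/SE)

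- b = 0: 5.0%
- b = 0.02 (10% of the planned difference): 6.2%
- b = 0.05 (25%): 12.8%
- b = 0.10 (50%): 36.8%
- b = 0.20 (100%): 90.1%

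These rates depend on the SE. If 292 per arm were spread evenly over four hospitals (73 each), the stated ICC of 0.05 would give a design effect of 1 + 72 × 0.05 = 4.6, an effective size of 292 / 4.6 = 63.5 and an SE of 0.102. The rates for b = 0.02, 0.05, 0.10 and 0.20 would then be 5.4%, 7.8%, 16.6% and 50.3%. The bias in the estimate is b in either case.

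**The case against.** The strongest reply is that a shared job title does not make the collectors the same people. The article speaks of implementers alongside research fieldworkers and uses a separately recruited facilitation team. Intervention recruitment ran from March 2017 with a further round in September 2017, while the follow-up survey is in 2018. Rosters and questionnaire order are also details that an article can leave to the full protocol and the instrument. This stands as far as it goes: overlap is an inference. It does not clear the point, because the article is not merely silent. It gives the invitation task to fieldworkers and carries the measurement procedure over unchanged.

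A second reply is that forms are self-completed, delivered in an envelope and numbered, that the scan is for completeness only, and that nobody in a read-aloud group speaks an answer. These features reduce fieldworker influence. They do not remove it, since the fieldworker may be present, receives the form back and leads the low-literacy sessions.

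A third reply is that trained staff know the desired answer whoever hands over the form. That is correct. Separating the roles removes the recruiter's contribution, not the whole demand effect.

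**Conclusion.** The point holds as a risk that the plan leaves open. If the same individuals recruit and collect, socially desirable reporting may be larger in the intervention arm. Its size is unknown. The rates above are conditional on assumed shifts and are not estimates.

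Two stronger readings are tempting and are not supported:

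- A reader might infer that demand effects fall on the intervention arm only. Neither the reach-and-appeal section nor the branded survey gifts are limited by arm, so controls may be cued too.
- A reader might multiply the 40–50% target by an assumed demand effect to get a share of the planned 0.20. With 0.1 to 0.3 SD and the control SD of 0.71, this gives 0.40 × 0.1 × 0.71 = 0.028 to 0.50 × 0.3 × 0.71 = 0.107, or 14% to 53%. With the intervention SD of 0.39 it gives 0.016 to 0.059, or 8% to 29%. Neither range can be relied on. The 40–50% is a training target and not the share approached by fieldworkers, leaders are invited at a meeting, and the effect size has no source in the documents. The sum also assumes that each of these respondents is surveyed by someone known to them as a recruiter.

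The problem is worth correcting because the remedy is cheap and can be applied before the follow-up survey. It does not by itself invalidate the trial.

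**What to change.** - For the follow-up survey, roster the existing fieldworkers so that nobody who recruited change agents or distributed campaign material at a hospital collects or reads out questionnaires there. Exchanging teams between hospitals would do this.
- In all eight hospitals, give the reach-and-appeal section, and any campaign-branded gift, only after the completed stigma scales have been handed in.
- State in the protocol who collects follow-up data and whether they had any intervention role at that hospital. If the teams are already separate, one sentence saying so settles the main point.

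The cost is some rostering and travel, a form split in two, and collectors who know the hospital less well when tracing baseline respondents. The article does not give the size of the fieldworker pool, so whether full separation is possible at every site cannot be checked here. The ordering of the form and gifts needs no extra people.

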#### The second SBCC intervention is a social marketing campaign promoting stigma reduction

Targeting all levels of staff, and all spaces in the hospital, the social marketing campaign is designed around one branded slogan and one branded image. The slogan (in three languages) says: *Let us Stop stigma. Be kind to yourself. Be kind to others*. This refers back to theory and the division of stigma into *internal* stigma (be kind to yourself) and *external* stigma (be kind to others). The image is very bold: a large open hand, positioned like a stop signal, in a red *shwe-shwe* design. *Shwe-shwe* is a traditional South African printed fabric much loved by people of all races and from all walks of life.

The slogan is repeated on different sized posters displayed throughout the different hospital wards, as well as administrative and meeting spaces. There is also a range of promotional gifts (pens; chocolates, wristbands; fridge magnets) branded with the same slogan and image, which we hand out to everyone in the facility.

Social marketing materials can be very short-lived in a recipient’s memory. This is why we have the same message and the same image communicated in different media and in different spaces, and why we hand out promotional gifts throughout the hospital on more than one occasion.

### Eligibility criteria for the interventions (SPIRIT point 10; see also ‘Section 3.3.1’)

To summarise, for the *clinical* intervention participants must either be occupational health unit staff, and, where occupation health units (OHUs), do not exist, physicians and nurses who test and treat facility staff for HIV and TB. Eligibility criteria for *attending the training workshops* are that participants who are recognised and nominated as change agents or potential change agents are selected by facility staff at all levels (not researchers) via two processes: positional sampling and snowball sampling.

Eligibility criteria for *facilitating the workshops* is that facilitators should be experienced and accredited by SAQA (South African Qualifications Authority). The facilitation team comprises of three such professionals, especially recruited, who, between them, can deliver the training in all three local languages.

### Criteria for discontinuing or modifying interventions, and for monitoring HCW actions

Participation in the interventions, as for the surveys, is voluntary and by consent, so participants can withdraw at any time without fear of prejudice (SPIRIT point 11b), and without fear of having their names reported in the workplace by the research or implementation teams.

In terms of the communication actions of HCW change agents, spontaneous and private conversations cannot be monitored or measured (SPIRIT point 11c). What we do is research their experiences, discussed later in the ‘Data collection’ section.

It is not anticipated that interventions will change at this point in time because they have already been extensively workshopped in collaborative meetings with all key FSDoH stakeholders, they have been piloted, the first in two series of training sessions has already been implemented in each of the four intervention hospitals (between June and July 2017), and the first set of social marketing materials has been distributed. The second series of training sessions is anticipated to take place between September and October 2017.

